### Resource use and costs

As already mentioned, data on resources used by the care-recipient of each study group will be obtained by an adapted version of the RUD instrument at baseline and after six months inclusion [18]. This RUD instrument attempts to include all resource use as defined by Drummond et al. [31] including: healthcare resource use containing hospital resources (f.e. in-patient and out-patient attendances), community care resources (f.e. general practitioner visits, nurse visits), caregiver and patient resources (f.e. time spent in caregiver), and resource use in other sectors (f.e. social worker visits, home help visits). Duration and frequency of the used services will be multiplied by each unit cost of the corresponding service. These unit costs will be obtained from the Belgian Reimbursement scheme using standard fees for regularly insured patients and other publicly available sources [18].

Time spent in caregiving will be calculated at baseline and after six months using the recall method for which also a part of the RUD instrument will be utilized. Next, the amount of time spent in caregiving will be monetized using the opportunity cost method which estimates the value of lost informal caregiver benefits due to spending time on providing informal care [35–37]. Productivity loss of the informal caregiver at productive age will not be taken into account because this would cause an overestimation due to double counting [31]. However, for caregivers at productive age we will gather information on whether their caregiving role effected their work situation.

During this trial, dyads of the intervention group will receive the intervention during five days for free. In normal circumstances patients must pay 65€ per day, while 350€ per day is covered by charity. However, to measure the total cost of the in-home respite care service under investigation in this trial, we will multiply the current unit cost of Baluchonnage per day (patient + charity) by the amount of days the in-home respite care was delivered. Additional costs above the fixed daily tariff - that patients must normally pay extra - will also be included such as: travel expenses during the respite period and having a pet (5€ extra per day) [33].

Additionally, willingness to pay for one day of in-home respite care by Baluchon will be obtained from both study groups using the contingent valuation method (CVM). This method can be defined as a stated preference method for eliciting a monetary value to a healthcare program. In this trial we use a closed response format [35, 36, 38–40].

Finally, for use in the decision analytic model, costs of nursing home placement will be derived from the average daily cost for staying in a nursing home in Belgium at the time of completing secondary endpoint.

### Within trial costs

Fixed intervention costs (f.e. program development, staff, and software) not changing based on the quantity of output, as well as variable costs (f.e. recruitment and assessment costs, intervention costs, and telephone and postage costs) varying on the quantity of output will be registered and then calculated into a total cost per caregiver/recipient dyad. Costs imposed by the study which are not part of routine practice will not be included in the cost analysis [31].

### Statistical analysis

First of all, descriptive statistics will be represented to draw a clear profile of the characteristics of study participants. Therefore the mean, percentages, and the standard deviations of quantitative variables will be displayed. To determine possible baseline differences between the groups, mean values of baseline characteristics will be compared using independent sample t-tests for continuous variables if normally distributed or by performing Pearson’s chi-square test for categorical variables. To help control for bias and confounding, statistical techniques such as propensity score matching will be used. Propensity score matching can be seen as a tool to simulate a RCT setting. In this way we can expect the observed effect to be an unbiased estimate of the real effect [41, 42].

To investigate possible effects of the intervention on the primary and secondary outcomes, analysis of variance will be conducted if the outcome variables are normally distributed. A *P*-value of 0.05 will be considered as significant. All analyses will be based on intention to treat also taking drop-outs into account and avoiding overestimation of respite care effects.

When the intervention is effective a cost-effectiveness analysis in a separate economic evaluation plan will be performed. ICERs will be calculated for the mean and upper and lower confidence levels of the costs and consequences. To explore uncertainty one-way-sensitivity analysis will be conducted around the ICER and illustrated in a Tornado diagram. Additionally, on all input variables a probabilistic sensitivity analysis, also called Monte Carlo analysis, will be conducted to test robustness of the model. These results will also be illustrated. Finally, the results and the willingness to pay threshold of the Belgian Health Care System will be presented in a cost-effectiveness acceptability curve [34].

To compare time to nursing home placement of persons who use respite care to those who do not, we will use Kaplan-Meier survival curves to illustrate association between the comparison groups. By additionally conducting a log-rank test statistical difference between the groups in time to placement can be found [43].

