### The in-home respite intervention

The in-home respite intervention group will receive in-home respite care also called “Baluchonnage” from Baluchon Alzheimer Belgium. Baluchon is a non-profit organization, founded in Québec by gerontologist [name]. She responded to the unmet need of many caregivers willing to take a break from caregiving duties, but lacking a solution for the person with dementia allowing them to stay home in their trusted environment. Eventually from this thought of mind, “Baluchonnage” was originated making it possible for those caregivers to take a short break while a trained support person (also called a “baluchonneuse” or “baluchonneur”) takes in their place. During this break, which can last up to two weeks, the caregiver has time to rest and return with new energy. For the person with dementia other resource use, structure, habits, and all daily activities remain the same. In this way Baluchon not only addresses to caregiver needs, but also to the need of the people with dementia feeling best in their trusted environment [7].

Twenty-four hours before the start of the respite period the “baluchonneur (se)” arrives at the home of the care-recipient. This transition period allows the “baluchonneur (se)” to get to know the environment, get to know the person with dementia and the caregiver, to build a trusting relationship, and to observe daily habits [7].

Additionally to the provision of respite, “Baluchonnage” also includes caregiver support by keeping a support diary during the respite period. In that diary the “baluchonneur (se)” writes down all daily experiences and strategies on how to manage the difficult behaviors the caregivers listed before. This support enables the caregiver to validate theirs perceptions, to learn how to deal with difficult behaviors and to feel understood by somebody. Even after the end of the respite period the “baluchonneur (se)” remains available for further counsel [7]. In Belgium this particular type of respite is not subsidized by the National Health Care Insurance.

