### Sample size

Sample size calculation was performed using SPSS SamplePower 3®. First, literature was searched to determine the needed effect size and standard deviation (SD) allowing to distinguish a statistical significant and clinical relevant difference in the primary outcome, i.e. burden. Based on the findings of a similar high quality intervention study an effect size of 0.4 was used in the analysis, which implies a difference of six points on the ZBI scale (Zarit Burden Interview), and a SD (standard deviation) of 15 [19]. Also, an average drop-out rate of 20% was taken into account, a power of 80% and a significance level at 0.05. Based on these values a total of 124 caregiver/care-recipient dyads will be needed for the intervention group.

To reduce selection-bias inherent to quasi-experimental studies an allocation ratio of 1:2 will be used to allow matching techniques. As a result 248 caregiver/care-recipient dyads will be needed in the control group.

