Despite the promising contribution of this study to community-based dementia care, several limitations need to be mentioned as well. First, there is a threat towards internal validity because the used quasi-experimental study design lacks random assignment of study groups. Although we use inclusion criteria to increase comparability and statistical efforts such as propensity score matching will be untaken, there can still be unmeasured confounders influencing causal inference. Nevertheless, for this particular research, a quasi-experimental design was preferable over a randomized controlled trial for feasibility and ethical reasons. First of all, the limited capacity of Baluchon Alzheimer Belgium makes it impossible to set up a RCT. Also, it can be seen as ethically unacceptable to randomly assign dyads to one of the trials arms. In this way some caregivers get free respite care while others cannot have this support during the trial.

Second, we only recruited caregivers asking for in-home respite care themselves in the intervention group and caregivers prepared to utilize this service in the control group. Therefore we cannot speculate whether effects might be different for caregivers not asking for or considering this type of support. Also, there is a high probability that caregiver/care-recipient dyads in the intervention group with lower socioeconomic status and lower educational level will be underrepresented because Baluchonnage is normally a rather expensive service that is not commonly known in Belgium. Nevertheless, we will use statistical techniques, such as propensity score matching, to respond to this problem. Also, the fact that participants receive the in-home respite care five days for free can also reduce the gap in socioeconomic status between intervention en control group.

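### Intervention dyads very probably share respite workers, but the sample size and the named analysis assume independence and no listed data item identifies the worker

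*Protocol article*

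**What the plan says.** The Sample size section uses "an effect size of 0.4 was used in the analysis", which it equates with "a difference of six points on the ZBI scale" and "a SD (standard deviation) of 15", together with "a power of 80% and a significance level at 0.05" and 20% drop-out. It concludes: "Based on these values a total of 124 caregiver/care-recipient dyads will be needed for the intervention group". Controls are then set at 248, a 1:2 ratio chosen to allow matching. No design effect is mentioned.

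Under Statistical analysis, the effect on primary and secondary outcomes is tested as follows: "analysis of variance will be conducted if the outcome variables are normally distributed". Propensity score matching is named as well. A worker or cluster term is not.

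The section on the in-home respite intervention describes a service "making it possible for those caregivers to take a short break while a trained support person" stands in for them. That person arrives a day early to build trust, keeps a diary of strategies for difficult behaviours, and can be consulted after the period ends. The Discussion adds that "the limited capacity of Baluchon Alzheimer Belgium makes it impossible to set up a RCT".

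Neither Table 1 nor Table 2 lists the worker's identity, and the described additions to the resource-use questionnaire do not include it.

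**The concern.** Part of this treatment is specific to the person who delivers it: the relationship, the strategies in the diary and the later advice. These bear on what is measured, namely burden, reactions to behavioural problems and the wish to institutionalize. Dyads served by the same worker may therefore have correlated outcomes. Controls do not receive the programme, so the design is partially nested, with clusters in one group and independent dyads in the other.

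An analysis that ignores such clustering understates the variance of the intervention mean. The P-value for the primary ZBI comparison is then too small and its interval too narrow. A demonstrated effect triggers the cost-effectiveness work and is meant to inform reimbursement, so a false positive would have consequences.

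A later analysis plan cannot repair this if nobody recorded which worker served which dyad.

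**Working it through.** **Inputs from the protocol article.** Difference 6 ZBI points, SD 15, power 80%, alpha 0.05, drop-out 20%, 124 intervention and 248 control dyads. Sidedness is not stated; two-sided reproduces the figure.

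**Inputs that are assumptions.** The number of workers, k, and the worker ICC are not in the document. I use k = 10 to 30 and ICC = 0.02 to 0.10.

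**Step 1: reproduce the stated size.** n per group = 2 × (1.96 + 0.8416)² × (15/6)² = 98.1, so 99. Allowing for drop-out, 99/0.8 = 123.75, so 124. The stated figure is the 1:1 calculation with independent observations, and 248 is its double.

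**Step 2: power without clustering.** Power = Φ(6/SE − 1.96).
- 99 v 99: SE = 15 × √(1/99 + 1/99) = 2.132, power 80.4%.
- 99 v 198 (248 × 0.8 = 198 evaluable controls): SE = 15 × √(1/99 + 1/198) = 1.846, power 90.1%.

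**Step 3: add a worker effect in the intervention group only.** With m = 99/k evaluable dyads per worker:
- Design effect: DE = 1 + (m − 1) × ICC
- Corrected standard error: SE = 15 × √(DE/99 + 1/n_c), with n_c = 99 or 198
- True error of the uncorrected test: 2 × Φ(−1.96 × SE without clustering / corrected SE)
- Power of a valid test: Φ(6/corrected SE − 1.96)

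For 15 workers and ICC 0.05: m = 6.6 and DE = 1 + 5.6 × 0.05 = 1.28. With 99 v 99, SE = 15 × √(1.28/99 + 1/99) = 2.276, which is 1.068 times 2.132.

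| Workers | ICC | DE | True error, 99 v 99 | Power, 99 v 99 | True error, 99 v 198 | Power, 99 v 198 |
|---|---|---|---|---|---|---|
| none shared | – | 1.00 | 5.0% | 80.4% | 5.0% | 90.1% |
| 30 | 0.02 | 1.05 | 5.3% | 79% | 5.4% | 89% |
| 20 | 0.05 | 1.20 | 6.2% | 76.6% | 6.5% | 86.3% |
| 15 | 0.05 | 1.28 | 6.6% | 75% | 7.2% | 85% |
| 10 | 0.05 | 1.45 | 7.6% | 72.1% | 8.5% | 81.4% |
| 10 | 0.10 | 1.89 | 10.3% | 65% | 12.0% | 73% |

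These use normal reference values. Small-sample degrees of freedom would lower power a little further.

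**Step 4: the design effect at which power falls to 80%.** The variance must satisfy DE/99 + 1/n_c = (0.4/(1.96 + 0.8416))² = 0.02039.
- 99 v 198: DE = (0.02039 − 1/198) × 99 = 1.52. That is an ICC of 0.52/8.9 = 0.058 with 10 workers, or 0.52/3.95 = 0.13 with 20.
- 99 v 99: DE = (0.02039 − 1/99) × 99 = 1.02, so there is almost no slack.

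Extra controls protect power but make the error inflation slightly worse, because the clustered group then contributes more of the total variance.

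**The case against.** The strongest reply is that the premise is inferred. No worker count, caseload, assignment rule or ICC is given, and limited capacity is stated of the organisation, not of a named pool of workers. This stands, so the point has to be conditional. The inference is nevertheless strong, since full independence would need a different worker for every one of 124 dyads.

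A reader might also infer that the stated 80% power is simply overstated. The document does not support that. If all 198 evaluable controls are used, power starts at about 90% and stays at or above 80% until the design effect exceeds about 1.52. Only a 1:1 matched comparison has no reserve, and the matching ratio in the analysis is not fixed. Even there, the loss at ICC 0.02 to 0.05 with 20 or more workers is only about 1 to 4 percentage points.

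Next, the analysis of variance is one sentence in a condensed article, and a worker term could sit in a plan that is not shown. That is fair as regards the model. It does not answer the sample size, which is stated in full and reproduces without a design effect, nor the data tables. The Discussion also considers what varies within the intervention group (duration, earlier use, other services) and leaves out the worker.

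Finally, the break lasts at most two weeks while the primary endpoint is at six months, with other support allowed in between. A worker effect could be diluted by then, and nothing in the document supports an ICC as high as 0.10. Repeat periods and earlier use are also allowed, so a dyad may have had more than one worker and simple nesting is an approximation. Both remarks stand. The first argues for the lower part of the range, and the second shapes the fix.

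**Conclusion.** The point holds in conditional form. The sample size assumes independent intervention dyads, the named analysis has no worker term, and the listed data would not allow one to be added. If workers are shared and the ICC is positive, the standard error for the primary comparison is too small.

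Under the assumed ranges this runs from negligible to a doubling of the error rate. The middle case of 15 workers and ICC 0.05 gives a true error of about 7% under either matching ratio, with valid power of 75% (99 v 99) or 85% (99 v 198).

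The document does not establish that workers are in fact shared, that the interval is certainly too narrow, or that the trial is underpowered. The point is worth acting on because the remedy is cheap and depends on data captured during the trial.

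**What to change.** 1. Record an anonymous worker code for each respite period, and report the number of workers and the dyads per worker.
2. Analyse ZBI and the other caregiver outcomes with a random intercept for worker in the intervention group only, using small-sample degrees of freedom, or with worker-clustered standard errors. Assign each dyad to the worker of its index study period. Add a sensitivity analysis for dyads that had several workers.
3. In the Sample size section, state that the calculation assumes no worker effect, and show power over a range of ICCs for both 1:1 and 1:2 matching.

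The cost is one extra data field, some analysis wording, a slightly wider interval and possibly a slightly lower stated power. These steps do not in themselves require more dyads. The document does not say whether the provider already holds the worker's identity in usable form, so this should be confirmed with it.

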### Cost-effectiveness analysis

When appropriate, i.e. if the intervention demonstrates an effect in the study endpoints, within-trial and modeled cost-effectiveness analyses will be conducted in a separate economic evaluation plan [31].

First the analysis will be performed from the perspective of the healthcare payer taking into account direct healthcare costs for the government’s healthcare budget (RIZIV/INAMI) as well as patients’ co-payments [32]. Assuming that policy makers would consider reimbursement of in-home respite care of the Baluchon type in the future, the daily cost of Baluchonnage will be included in the analyses [33]. Alongside the costs of Baluchonnage other costs of healthcare resource use including hospital, residential, and community care will be included [31].

Additionally, also a full societal viewpoint will be undertaken not only including potential direct healthcare costs for the healthcare budget and patients, but also all other direct and indirect costs for caregivers and patients. Because in this viewpoint everyone affected by the intervention should be considered, caregiver time and costs (f.e. time spent in caregiving, productivity loss) as well as resource use and costs of other sectors (f.e. food delivery) should be included.

Based on the KCE guidelines (Belgian Health Care Knowledge Centre) for health economic evaluations in Belgium future costs will be discounted at 3% and future QALY’s at 1.5% [32]. Health utilities or QALY’s of caregivers from both intervention arms will be derived from the Belgian public preference list based on scores on the EQ-5D [34].

Decision analytic modeling will be carried out to extrapolate effects of the intervention found in the trial to a longer time horizon. The model will be based on the results from the trial as well as existing data from literature. Assumptions, hypotheses, and sources of information will be represented in a transparent and clear way. Finally, the model will be validated by experts.

The incremental cost-effectiveness ratio (ICER) will be calculated using the following equitation [34]:$$ \begin{array}{l}\mathrm{ICER} = \underline {\Delta \mathrm{COSTS}}\left( difference\  between\  mean\  total\  cost\  of\  in tervention\  group\  and\  control\  group\right)\\ {}\kern4em \Delta \mathrm{QALYs}\left( difference\  between\  mean\  in\  QALY's\  of\  in tervention\  group\  and\  control\  group\right)\end{array} $$

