To measure differences in quality of life of caregivers, QALYs will be obtained from the EQ-5D. It is known that this generic preference-based measure of health lacks sensitivity in determining differences especially in emotional and mental health problems, and even more in short periods. Because it is to be expected from this intervention that in particular those emotional and mental health dimensions will shift, the question can be asked if the EQ-5D will be sensitive enough to show an effect on such short notice. Still, its use is preferred over the use of other disease-specific instruments, which have proven to be more sensitive, because the developed algorithms to translate the obtained scores into health utilities have been subject to a lot of criticism in literature.

Despite the described limitations, inherent to the complex nature of investigating respite care services, this study will have great added value because to date no studies measured effectiveness and cost-effectiveness of an in-home respite service similar to the Baluchon service. Results of this trial can give much more insight in potential benefits and disadvantages of community-based respite care, especially for informal caregivers and the healthcare system, but also for care-recipients. Conclusions based on this trial can thus help policy-makers in considering future directions of dementia care.

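### ICERs at the separate confidence limits of costs and QALYs are not a valid uncertainty range, and no joint method is stated for the within-trial ICER

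*Protocol article*

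**What the plan says.** The Cost-effectiveness analysis section states that "The incremental cost-effectiveness ratio (ICER) will be calculated" as the difference in mean total cost divided by the difference in mean QALYs. It covers two analyses: "within-trial and modeled cost-effectiveness analyses will be conducted in a separate economic evaluation plan".

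On uncertainty, the Statistical analysis section lists four elements:

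- A limit-based step: "ICERs will be calculated for the mean and upper and lower confidence levels of the costs and consequences".
- A step that varies one input at a time: "To explore uncertainty one-way-sensitivity analysis will be conducted around the ICER and illustrated in a Tornado diagram".
- A Monte Carlo step: "on all input variables a probabilistic sensitivity analysis, also called Monte Carlo analysis, will be conducted to test robustness of the model".
- A display in which the results and "the willingness to pay threshold of the Belgian Health Care System will be presented in a cost-effectiveness acceptability curve".

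The work is conditional: "When the intervention is effective a cost-effectiveness analysis in a separate economic evaluation plan will be performed". QALYs come from the caregiver's EQ-5D, which Tables 1 and 2 schedule at baseline and six months only. The Discussion doubts the instrument over so short a period: "the question can be asked if the EQ-5D will be sensitive enough to show an effect on such short notice".

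**The concern.** A ratio computed at the separate limits of its numerator and denominator has three faults.

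- **No joint distribution.** Each limit comes from a marginal interval, so the correlation between a dyad's costs and QALYs plays no part and the resulting range has no known coverage.
- **Undefined pairing.** The sentence does not say whether the lower cost limit goes with the lower or the upper QALY limit. The two choices give different ranges.
- **Failure near zero.** If the QALY limits lie on either side of zero, one of the two ratios is negative and the other positive when costs are higher, and the span between them need not contain the point estimate.

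A QALY difference near zero is realistic here. The Discussion questions the sensitivity of the EQ-5D, and the condition for running the economic analysis is an effect in the study endpoints, which an effect on burden alone could meet.

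Cost-effectiveness is one of the stated research questions, and the Discussion links the result to reimbursement. A negative ICER at the lower QALY limit means higher cost with a worse outcome, but it could be misread as the programme dominating usual care.

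**Working it through.** **The plan's own figure.** The article gives no number for the ICER, its interval or the QALY difference. Its one design calculation reproduces. A 6-point difference with SD 15, two-sided 0.05 and 80% power needs 99 per group. 99/(1 - 0.20) = 123.75, so 124, and 2 x 124 = 248 controls. After 20% drop-out about 0.8 x 124 = 99 and 0.8 x 248 = 198 dyads remain, before any loss through matching.

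**Cost difference.** From Resource use and costs: 65 + 350 = EUR 415 per day, and 5 x 415 = EUR 2,075. Assumed: five days for every dyad and no offsetting savings.

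**Scale of the QALY difference.** With two measurements and linear interpolation, QALY = 0.5 x (u0 + u6)/2 = 0.25 x (u0 + u6). With equal baselines, a utility gain of 0.04 at six months is 0.25 x 0.04 = 0.01 QALY.

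**Illustration 1, cost held fixed.** Assumed: utility SD 0.2 at each time and correlation 0.6.

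- SD of QALY = 0.25 x sqrt(0.04 + 0.04 + 2 x 0.6 x 0.04) = 0.0894.
- SE = 0.0894 x sqrt(1/99 + 1/198) = 0.0110.
- QALY limits = 0.01 ± 1.96 x 0.0110 = -0.0116 and 0.0316.
- Point ICER = 2,075/0.01 = EUR 207,500.
- At the upper limit: about EUR 65,700. At the lower limit: about EUR -179,000.

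The point estimate lies outside this range. The result depends on the SE. If QALYs were adjusted for baseline utility, the residual SD would be 0.25 x 0.2 x sqrt(1 - 0.36) = 0.04 and the SE 0.0049. At 0.01 QALY the lower limit would then be 0.00035, just above zero, with an ICER there of about EUR 5.9 million. At 0.005 QALY the limits, -0.0047 and 0.0147, would still include zero.

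**Illustration 2, costs varied as the sentence requires.** Assumed: QALY SD 0.10 and cost SD EUR 6,000. The cost limits are 2,075 ± 1.96 x 6,000 x sqrt(1/99 + 1/198) = EUR 627 and 3,523.

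| QALY difference (limits) | Point ICER | Low cost/high QALY; high cost/low QALY | Low/low; high/high |
|---|---|---|---|
| 0.01 (-0.0141, 0.0341) | 207,500 | 18,386; -249,368 | -44,418; 103,222 |
| 0.05 (0.0259, 0.0741) | 41,500 | 8,465; 136,142 | 24,250; 47,521 |

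At 0.01 both ranges exclude the point estimate. At 0.05 both contain it, but one is 127,677 wide and the other 23,271.

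**Coverage.** Simulation used bivariate normal differences, 400,000 draws per scenario, QALY SD 0.08 or 0.12, cost SD EUR 6,000, cost-QALY correlation -0.3 to 0.3, and 99 and 198 dyads. The range is the span between the two values.

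| True QALY difference | QALY limits include zero | Coverage of the true ICER |
|---|---|---|
| 0.005 to 0.02 | 47-94% of trials | 4-53%, either pairing |
| 0.10 | practically never | 98-100% (opposed pairing), 67-86% (matched pairing) |

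Fieller's joint interval covered about 95% throughout, although for small QALY differences it can be unbounded or in two parts.

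**The case against.** Two stronger readings are tempting. The first is that the limit-based ICERs are the plan's whole treatment of uncertainty. They are not: three other elements follow in the same paragraph, and the words about exploring uncertainty introduce the one-way analysis. The second is that the plan presents these values as a confidence interval. It never calls them that.

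The acceptability curve also deserves credit. A curve built on joint replicates handles cost-effect uncertainty and does not fail near a zero QALY difference, and it is not expressly confined to the model. The model is itself to draw on trial results, so trial estimates are among its inputs. But the only joint distribution named as a possible source for the curve is the Monte Carlo analysis, which is tied to the robustness of the model. A one-way tornado diagram cannot carry correlation. Adding sound displays does not make the limit-based values sound.

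It can also be said that the detail belongs to a separate economic plan that is not shown. Silence on a bootstrap would then be no fault, and that part stands. The criticised sentence, however, is a stated method and not an omission. If the separate plan follows it, the problem carries over; if not, the article and that plan disagree.

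Finally, the illustrations rest on assumed SDs, correlations and differences. The failure near zero is a property of the ratio, but how often it would occur here depends on those inputs.

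**Conclusion.** The point holds in a limited form. ICERs at separate limits of costs and consequences are not a valid uncertainty range, and they are the only sampling-uncertainty step stated for the within-trial comparison.

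How badly they behave depends on the QALY difference. Under the assumptions shown, they can exclude their own point estimate at about 0.01 QALY. At 0.05 they contain it, with a width that depends on the unstated pairing. The documents supply only the daily cost, the planned group sizes and the drop-out rate. The QALY and cost SDs, the correlations and the QALY differences are assumptions.

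A reader might infer that the whole economic result, or the trial's main conclusion, is undermined. The documents do not support that. Other uncertainty analyses are planned, the economic work is conditional and secondary, and the burden comparison and sample size are untouched. Severity is minor to moderate.

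**What to change.** Replace the sentence on ICERs at confidence levels with wording such as: Sampling uncertainty in the within-trial analysis will be assessed by a non-parametric bootstrap of dyads, with each dyad's cost and QALY resampled together and the propensity-score step handled within the resampling or by an appropriate variance method. Results will be shown on the cost-effectiveness plane and as incremental net monetary benefit with a 95% confidence interval.

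State that the acceptability curve already planned will, for the within-trial analysis, be built from these replicates, and keep the probabilistic analysis for the decision model. Carry the same wording into the separate economic plan, or confirm that it already says this.

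The cost is a change of wording and a little extra analysis work. No additional data are needed.
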